## Abstract

**Methods::**

This randomized controlled trial (RCT) will be carried out in Hangzhou TCM Hospital Affiliated to Zhejiang Chinese Medical University planning to recruit 180 infertile patients undergoing IVF-ET with the type of deficiency of both the spleen and kidney. The control group will be treated by conventional western medicine and the treatment group will use conventional western medicine plus Jian-Pi-An-Tai formula. The primary outcomes will include Embryo implantation rate, Clinical pregnancy rate, Persistent pregnancy rate; and the secondary outcomes will include TCM symptom score and reproductive hormones. Safety evaluation will be recorded during the whole study. All data in this RCT will be analyzed by SPSS 23.0 software. This study has been approved by the Research Ethics Committee of the Hangzhou TCM Hospital Affiliated to Zhejiang Chinese Medical University (2022KY130).

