### 2.6. Outcome measures

#### 2.6.1. Primary outcome measures

Embryo implantation rate: number of embryos implanted/total number of embryos transferred * 100%. Blood sampling test of β-HCG will be taken on the 8th and 10th days after embryo transfer. Positive results can be determined as successful embryo implantation.Clinical pregnancy rate: number of clinical pregnancies/number of implanted embryos * 100%. Doppler ultrasound will be taken on the 5th week after embryo transfer. Gestational sac and fetal heart beat can be determined as successful clinical pregnancy.Persistent pregnancy rate: number of cycles of continuous pregnancy/number of embryos implanted * 100%. Doppler ultrasound will be taken on the 12th week after embryo transfer. Existence of fetal heart beat can be determined as successful persistent pregnancy.

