### 2.9. Statistical analysis

The statistical analysis of this study will be conducted by statisticians of the Zhejiang Chinese Medical University. Software packages SPSS 23.0 and SAS 9.3 will be used for statistical analysis. All statistical tests will be conducted by 2-sided tests and *P* values less than .05 are considered statistically significant. The description of quantitative indicators will calculate the number of cases, mean, standard deviation, median, minimum and maximum. Classification indicators are described by the number of cases and percentages of each category. Normally distributed data is represented by mean ± standard deviation, and non-normally distributed data is represented by median and interquartile range. Comparisons between groups of measurement data will be conducted by using independent sample *t* test, and within group differences will be tested with paired *t* test. Differences between groups of numeration data will be assessed with chi-square test.

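### Three unranked primary outcomes are each tested at two-sided 0.05, so if any one may carry the efficacy claim the familywise error is about 8% to 13%, not 5%

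*Protocol article*

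**What the plan says.** The abstract lists the primaries together: "The primary outcomes will include Embryo implantation rate, Clinical pregnancy rate, Persistent pregnancy rate". Section 2.6.1 defines them:

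- "Embryo implantation rate: number of embryos implanted/total number of embryos transferred * 100", judged by β-HCG on days 8 and 10 after transfer.
- "Clinical pregnancy rate: number of clinical pregnancies/number of implanted embryos * 100", judged by ultrasound at week 5.
- "Persistent pregnancy rate: number of cycles of continuous pregnancy/number of embryos implanted * 100", judged by ultrasound at week 12, where "Existence of fetal heart beat can be determined as successful persistent pregnancy".

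None is called the main outcome. No order of testing is given, and nothing says whether one, two or all three must be significant for the trial to succeed.

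Section 2.9 sets one rule for all analyses: "All statistical tests will be conducted by 2-sided tests", and P "values less than .05 are considered statistically significant". For rates, "Differences between groups of numeration data will be assessed with chi-square test". Section 2.8 uses a single alpha of 0.05 for one comparison and does not divide it. No multiplicity adjustment appears in the article.

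**The concern.** With three co-equal primaries and an unadjusted threshold for each, the trial has three chances to produce a significant primary result when the formula has no effect. The article's 0.05 then describes each test but not the primary conclusion as a whole.

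The three outcomes also differ in clinical weight. The introduction states the aim as efficacy and safety for the pregnancy outcome of IVF-ET. Implantation is read from a blood test about a week after transfer, and persistent pregnancy from a heartbeat at week 12. Without a ranking, a result significant only on the early blood test could be reported as a met primary outcome with no gain at week 12. The trial is also unblinded, which makes it more useful to fix the success criterion in advance.

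**Working it through.** **Inputs from the article.** Three primary outcomes (abstract, 2.6.1); two-sided 0.05 for each and chi-square for rates (2.9); 180 women in two groups and 10% dropout (2.8).

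**Assumed inputs.** Allocation is taken as 1:1, so 90 per arm, or 90 × 0.9 = 81 evaluable. The article gives no implantation or pregnancy rates. Those used were implantation 0.4 to 0.6, clinical pregnancy given implantation 0.8 to 0.9, and persistence given clinical pregnancy 0.85 to 0.95.

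**Step 1. The plan's own figure.** The article gives no familywise error to reproduce. Its only related figure is the sample size: 86.2% v 54.2%, alpha 0.05, power 80%. The usual two-proportion formula, two-sided, is

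n = [1.96 × √(2 × 0.702 × 0.298) + 0.842 × √(0.862 × 0.138 + 0.542 × 0.458)]² / 0.32² = 31 per arm.

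That is 62 in total and 70 after 10% dropout, so 180 is not reproduced. This is a separate matter and does not affect the error calculation. Those rates are for an overall response, which is none of the three primaries.

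**Step 2. Reference values.**

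- Three independent tests: 1 − 0.95³ = 14.3%.
- General upper bound, whatever the correlation: 3 × 0.05 = 15%.
- Benefit direction only, independent tests: 1 − 0.975³ = 7.3%, against 2.5% for one test.

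**Step 3. Simulation with no treatment effect.** In each arm, implanted ~ Bin(n, p₁), clinical ~ Bin(implanted, p₂), persistent ~ Bin(clinical, p₃). There were three chi-square tests without continuity correction and 300,000 replicates per scenario. Chance of at least one significant result in either direction, n = 90 per arm:

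| p₁, p₂, p₃ | Women as common denominator | Implanted as denominator for outcomes 2 and 3 |
|---|---|---|
| 0.4, 0.8, 0.85 | 9.5% | 13.2% |
| 0.5, 0.8, 0.9 | 9.0% | 12.0% |
| 0.6, 0.85, 0.9 | 8.9% | 13.0% |
| 0.5, 0.9, 0.95 | 7.6% | 12.0% |

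Each test on its own rejects in 4.4% to 5.3% of these replicates, so the excess comes from the number of tests. Further runs over similar rates reached 10.0% and 13.6% for the two columns.

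The columns differ for a simple reason. With women as the common denominator, the three outcomes are nested and strongly correlated. With implanted embryos as the denominator, outcomes 2 and 3 condition on implantation. The first test is then nearly independent of the other two, which remain correlated with each other.

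**Step 4. Unit of implantation.** Section 2.3.1 requires two transferred embryos, so the first denominator is about 2 × 90 = 180 embryos per arm. With n = 180 and implanted denominators, the same four scenarios give 12.45% to 12.73%. The conclusion does not move. Embryos are treated as independent here; a plain chi-square on two embryos per woman could raise the error further, but that was not quantified.

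**Step 5. Direction.** Counting only false results in favour of the formula (positive-test rate 0.5 to 0.6, conditional rates 0.8 to 0.9 and 0.85 to 0.93), the chance is 4.0% to 5.0% with women as denominator and 5.9% to 6.9% with implanted denominators.

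**Step 6. After correction.** At 0.05/3 = 0.0167 per test, the familywise error is 1 − (1 − 0.0167)³ = 4.9% if independent, and 2.6% to 4.6% in the simulations. Holm has the same error when all three nulls are true. One primary outcome, or a fixed order, holds it at 5%.

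**The case against.** The strongest objection is that the any-one-of-three rule is inferred. A reader might take the article to say that a positive β-HCG result alone makes the trial a success. It does not say that: section 2.9 only defines when a single test is significant. Silence is equally compatible with requiring all three, and under that rule there is no inflation. This stands, so the error figures are conditional on the any-one reading.

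Second, multiplicity is often handled in a statistical analysis plan, which is not shown, and an article condenses its protocol. This stands only in part. The article is not silent on the threshold: it applies an unadjusted 0.05 to all tests while naming three co-equal primaries. An adjustment elsewhere would have to depart from that rule as written.

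Third, a reader might infer that the chance of wrongly claiming efficacy is well above 5%. It is not: the 8% to 13% counts false results in both directions. False claims of benefit run at about 4% to 7%, still well above the 2.5% of a single test. Likewise, 14.3% is the value for independent tests; it is neither this trial's error rate nor the general ceiling.

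Fourth, a reader might conclude that 180 women are too few once alpha is split. The article's own rates do not support this. At 0.0167 the formula gives 42 per arm, or 47 per arm (94 in total) after dropout.

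**Conclusion.** The point holds in conditional form. The article fixes three unranked primary outcomes and an unadjusted two-sided 0.05 for each. If significance on any one may support efficacy, the familywise two-sided error is about 8% to 10% with women as denominator and about 12% to 13% with the implanted-embryo denominators. A false claim of benefit then has a probability of about 4% to 7%, against 2.5% for one test.

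The sizes rest on 1:1 allocation, the assumed rates and independent embryos. The direction does not depend on the particular rates: every scenario examined lies above the nominal level for a two-sided result. The conclusion would fall away only if all three outcomes had to succeed, or if an order or adjustment were fixed in advance, and the article states neither. Which denominator the second and third outcomes should use is a separate matter.

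**What to change.** Amend sections 2.6.1 and 2.9, and the abstract to match, in one of two ways, before outcome data are examined.

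1. **One primary outcome.** Designate a single primary, tested at two-sided 0.05. Persistent pregnancy at week 12 is the natural candidate given the stated aim, though this choice is partly one of preference. Test the other two in a stated order, for example clinical pregnancy and then implantation, each only if the one before it is significant.
2. **Three primaries with Holm.** Compare the smallest P value with 0.05/3 = 0.0167. If it is significant, compare the next with 0.05/2 = 0.025, and then the last with 0.05. Stop at the first non-significant result.

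**Cost.** The sponsor can no longer claim success on an early marker alone at an unadjusted 0.05. Under option 1, a non-significant primary leaves the other two without a confirmatory test. Holm costs some power per outcome. With 81 evaluable per arm and the article's rates, power at the strictest step falls from 99.6% to 98.6%. From a 54.2% control rate, the smallest difference detectable with 80% power at that step rises from about 20.9 to 23.9 percentage points. Those rates belong to the overall response, so they are only a guide for the three primaries. On them, no additional participants are needed.

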**Discussion::**

The results of this RCT will contribute to provide scientific and rigorous evidence for the efficacy and safety of Jian-Pi-An-Tai formula in treating infertile women undergo IVF-ET. And the results from this RCT will be published in a relevant journal after finished.

## 1. Introduction

Couples who have a normal sexual life but do not conceive naturally for more than a year are considered to have infertility. Infertility has become the third most serious disease, making it a global public health issue.^[1]^ Numerous factors, including hormonal imbalance, genetics, diet, smoking, caffeine use, and alcohol consumption, are linked to infertility. In vitro fertilization and embryo transfer (IVF-ET) is widely performed as an infertility treatment worldwide, resulting in the births of more than 5 million infants worldwide.^[2]^ Despite the remarkable advancements in assisted reproductive technology (ART), a significant number of infertile women continue to experience serial implantation failure, despite the high quality of the transferred embryos. In addition, women conceived through IVF-ET have a higher rate of threatened abortions than natural pregnancy.^[3]^ It is crucial to improve the implantation rate and reduce the abortion rate after embryo transfer for the success of IVF-ET.

The process of embryo implantation, which involves both the embryo and the mother’s endometrium, is intricate. One of the main causes of unsuccessful embryo implantation is assumed to be impaired endometrial receptivity.^[4]^ A healthy pregnancy is built on a foundation of appropriate implantation processes, which are facilitated by optimal receptivity. Endocrine reasons, inflammatory events, thin endometria, fibroids, polyps, septa, and immunologically induced abnormalities are only a few of the contributing elements that affect receptivity. Although implantation failure in IVF-ET is a very common occurrence, there are currently no evidence-based therapeutic treatments available. Therefore, current therapy approaches are mostly empirical, based on some biologic justification, but have scant clinical proof to back them up.^[5,6]^

Chinese herbal medicines have been widely used in Asian countries for millennia to treat a variety of reproductive problems, and they hold promise for the future of human reproductive health, notably in the treatment of recurrent miscarriage and ART drugs.^[7]^Numerous clinical and experimental studies have demonstrated the effectiveness of the traditional Chinese medicine in the prevention and treatment of recurrent spontaneous abortion, in increasing the number and quality of high-quality embryos, in repairing endometrium, and in improving uterine receptivity.^[8–11]^ The spleen and kidney are the foundation of acquired constitution and congenital constitution respectively. Along with the spleen, the spleen governs transportation and transformation, generating qi and blood for the entire body. The main cause of the embryo’s failure to develop normally is deficiency of both the spleen and kidney.

Jian-Pi-An-Tai formula is an experience formula in treating threatened abortion (Deficiency of both the spleen and kidney type) for more than 50 years in our team. In recent years, Jian-Pi-An-Tai formula has also been used to treat infertile women after embryo transfer and shows superiority compared to single use of conventional western medicine. However, the of evidence on its effective in treating infertile women undergo IVF-ET is lacking. Therefore, the aim of this study is to verify the clinical efficacy and safety of Jian-Pi-An-Tai formula for the pregnancy outcome of IVF-ET in infertile women.

## 2. Methods

### 2.1. Trial design

This study is a protocol for a randomized, non-blinded, controlled clinical trial. A total of 180 infertile patients with the type of Deficiency of both spleen and kidney will be conducted according to the flow diagram and will last for near 2 years, scheduled to start from January 2023 (Fig. 1).

**Figure 1. F1:**
[figure not shown]
Study flow chart.

### 2.2. Ethics committee

The study will follow the human research regulations of the Research Ethics Committee of the Hangzhou TCM Hospital Affiliated to Zhejiang Chinese Medical University, under the process number 2022KY130. After all aspects of participation in the research have been clarified, participants are required to sign a written informed consent form. One of the researchers responsible for the procedures will explain the consent forms. The study will be carried out in accordance with the Declaration of Helsinki. The study participants will be recruited at Run Run Shaw Hospital affiliated to Zhejiang University and treated at the Hangzhou TCM Hospital Affiliated to Zhejiang Chinese Medical University, from January 1, 2023 to October 31, 2024.

### 2.3. Participants

#### 2.3.1. Inclusion criteria.

Patients who meet the diagnostic criteria for infertility and spleen kidney deficiency syndrome;Patients who plan to perform ART in the Reproductive Department of Run Run Shaw Hospital affiliated to Zhejiang University and plan to perform frozen embryo transfer; the transferred embryos are 2 superior embryos;25 to 40 years old;Patients who have been insured in Hangzhou TCM Hospital Affiliated to Zhejiang Chinese Medical University after embryo transfer;Signed informed consent.

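### With two embryos transferred to every woman, the primary outcome formulas credit twins inconsistently, and no outcome or safety item identifies multiple pregnancy

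*Protocol article*

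**What the plan says.** All references are to the protocol article.

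- **2.3.1 Inclusion criteria** requires that "the transferred embryos are 2 superior embryos".
- **2.6.1 Primary outcome measures** defines three rates:
  - Embryo implantation: "number of embryos implanted/total number of embryos transferred". It is ascertained by blood β-HCG on days 8 and 10 after transfer: "Positive results can be determined as successful embryo implantation".
  - Clinical pregnancy: "number of clinical pregnancies/number of implanted embryos * 100". It is ascertained by ultrasound in week 5: "Gestational sac and fetal heart beat can be determined as successful clinical pregnancy".
  - Persistent pregnancy: "number of cycles of continuous pregnancy/number of embryos implanted * 100". "Doppler ultrasound will be taken on the 12th week after embryo transfer", and a fetal heart beat at that scan is the criterion.
- **2.6.2 Secondary outcome measures** lists the TCM symptom score and reproductive hormones.
- **2.7 Safety evaluation** lists liver function and routine blood tests. The Abstract adds only that safety is recorded throughout the study.

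Twin or multiple pregnancy is not mentioned in any of these sections.

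**The concern.** When two embryos are transferred, a treatment can raise the number of implanted embryos in two ways: more women become pregnant, or more pregnant women carry twins. These are different results for a trial whose Introduction sets out to verify efficacy and safety for the pregnancy outcome. The listed outcomes cannot separate them.

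The formulas also mix units. The first counts embryos over embryos. The other two count pregnancies or cycles over embryos. The test that supplies the embryo count gives one positive or negative result per woman. A difference between arms in the share of twins could therefore look like a gain on one primary outcome and a loss on the other two, with nothing among the listed outcomes to show the reader why.

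**Working it through.** **Inputs.** From the document: two embryos per woman (2.3.1), the three formulas (2.6.1), and 180 women in two groups (2.8). Assumed: equal allocation, so 90 women and 180 transferred embryos per arm; the numbers pregnant; the twin shares; and no losses between implantation and the scan. The article gives no implantation rate or twin rate, so there is no figure of its own to reproduce on this point.

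**Step 1. Credit given to one pregnant woman by the printed formulas**

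| Primary outcome | Singleton | Twin |
|---|---|---|
| Implantation (embryos / embryos transferred) | 1/2 | 2/2 |
| Clinical pregnancy (pregnancies / implanted embryos) | 1/1 | 1/2 |
| Persistent pregnancy (cycles / implanted embryos) | 1/1 | 1/2 |

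**Step 2. Same number of pregnant women, different twin share.** Let 45 of 90 women be pregnant in each arm (50.0% in both), and let t be the twin share of pregnancies. Implanted embryos = 45 × (1 + t).

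- Control, t = 20%: 45 × 1.2 = 54. Implantation 54/180 = 30.0%. Clinical pregnancy 45/54 = 83.3%.
- Treatment, t = 40%: 45 × 1.4 = 63. Implantation 63/180 = 35.0%. Clinical pregnancy 45/63 = 71.4%.

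Other assumed shares (expected values):

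| Twin share, control vs treatment | Implantation | Clinical pregnancy |
|---|---|---|
| 10% vs 40% | 27.5% vs 35.0% | 90.9% vs 71.4% |
| 20% vs 40% | 30.0% vs 35.0% | 83.3% vs 71.4% |
| 20% vs 50% | 30.0% vs 37.5% | 83.3% vs 66.7% |

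If every pregnancy continues to week 12, the persistent rate equals the clinical rate.

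The plan's chi-square test, without continuity correction and with embryo counts rounded to whole numbers, gives for implantation and clinical pregnancy respectively: P = 0.14 and 0.015 (10% vs 40%), 0.31 and 0.13 (20% vs 40%), 0.12 and 0.032 (20% vs 50%). An artificial loss on clinical pregnancy can thus cross the .05 threshold when exactly as many women are pregnant in each arm.

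**Step 3. If each β-HCG-positive woman is counted once.** Implanted = 45 in both arms, whatever the twin share. Implantation is 45/180 = 25.0% and clinical pregnancy 45/45 = 100% in both arms. Twins become invisible, and the implantation rate cannot exceed 90/180 = 50%. The formula and the test therefore give different answers from the same data.

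**Step 4. A treatment that does help.** Let per-embryo implantation rise from 35% to 45%, that is, from 70 to 90 embryos per 100 women.

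- If the two embryos implant independently, pregnant women = 1 − (1 − p)²: 57.75% rises to 69.75%. Twins = p²: 12.25% rises to 20.25% of transfers. Clinical pregnancy by the printed formula is 0.5775/0.70 = 82.5% against 0.6975/0.90 = 77.5%: it falls although 12 more women per 100 are pregnant.
- If all 20 extra embryos go to women who would otherwise have had none, pregnant women rise to 57.75 + 20 = 77.75 per 100, twins do not change, and clinical pregnancy is 77.75/90 = 86.4%: it rises.

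The same implantation gain gives opposite movements on the second primary outcome, depending only on the twins.

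**The case against.** A reader might infer something stronger: that the plan scores a twin as full or double success on every primary outcome, so that a gain made partly of twins would be reported as pure benefit. The document does not support that. Two of the three rates have implanted embryos as denominator, so read literally they penalise twins. Calling a twin a full success there means replacing the denominator with women or transfers, which the article does not do. Even the double credit on implantation needs an embryo count that β-HCG does not supply.

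Nor does it follow that higher per-embryo implantation must bring more twins. The second case in step 4 shows a rise with none. Under independence, the share of the gain made of second embryos would be 8 of 20 (40%) for 35% to 45%, but that figure rests wholly on the independence assumption and on rates that appear nowhere in the article.

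It can also be said that the article condenses a fuller protocol, that ultrasound is already scheduled, and that the number of sacs may be recorded in a form not shown here. That is fair as far as recording goes: the document does not say the count will be left out. It does not remove the point, because the article sets out its primary formulas, secondary outcomes and safety items explicitly, and those formulas, followed as printed, contradict one another. That the article attributes no particular risk to multiple pregnancy is also true. The scoring problem does not depend on it.

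**Conclusion.** The point holds in this form: two-embryo transfer is required, multiple pregnancy is not among the outcomes or safety items, and the three primary rates treat a twin as worth twice, half and half of a singleton. The credits in step 1 follow directly from the printed formulas.

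The size is illustrative. With equal numbers pregnant and twin shares of 20% against 40%, implantation shifts by +5.0 percentage points and clinical pregnancy by −11.9 (71.4 − 83.3). Over the other shares tried, the shifts are +7.5 on implantation, and −19.5 (10% vs 40%) and −16.7 (20% vs 50%) on clinical pregnancy. These rest on assumed pregnancy numbers, assumed twin shares, equal arms and no losses before the scan. The likely result is contradictory primary outcomes that cannot be explained from the listed data, rather than a one-sided overstatement of benefit. This should be corrected before the outcomes are analysed.

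**What to change.** In section 2.6:

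1. Record the number of gestational sacs and fetal heart beats at the week-5 scan, and the number of fetal heart beats at the week-12 scan.
2. Define clinical and persistent pregnancy per randomised woman, and report each by arm, split into singleton and multiple.
3. If a per-embryo implantation rate is kept, take its numerator from an embryo count such as the sacs on the scan, and report β-HCG positivity separately, per woman.

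In section 2.7, list multiple pregnancy as a safety outcome, by arm.

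The cost is one field on the form at scans already planned, and one table. Nothing in treatment or in the number of embryos transferred changes. The downside is that the efficacy message may look less favourable once singleton and multiple pregnancies are shown apart.
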